### Measures

At each time point, data will be collected online through the Sojump platform, an internet-based survey application that is widely used in mainland China, and Tencent Meeting. Participating families will be provided with child assessment feedback to promote retention.

#### Primary outcome

The primary outcome of interest, pre-schoolers’ sleep behaviours, will be measured using the Chinese version of the Children’s Sleep Habit Questionnaire (CSHQ) [21, 22]. The CSHQ is a parental-report instrument, consisting of 33 items for scoring and several extra items intended to provide useful information about the child’s sleep behaviours [21]. The 33 items are grouped into eight subscales, measuring different aspect of sleep including: 1) bedtime resistance, 2) sleep-onset delay, 3) sleep duration, 4) sleep anxiety, 5) night wakings, 6) parasomnias, 7) sleep-disordered breathing, and 8) daytime sleepiness [21]. This instrument has shown to be reliable (Cronbach’s alpha: 0.68 to 0.78; test–retest reliability: 0.62 to 0.79) and valid (sensitivity = 0.80, and specificity = 0.72) for use in children aged 4 to 10 years [21]. A previous study further validated this instrument in children aged 2 to 5.5 years and observed significant correlations with small to large effect size between CSHQ and actigraph measures of sleep onset time (*r* = 0.48), night waking duration (*r* = 0.21), total 24-h sleep duration (*r* = 0.25), and morning awake time (*r* = 0.62) [23]. The Chinese version of the CSHQ has demonstrated good reliability (overall Cronbach’s alpha = 0.73; overall test–retest reliability = 0.85) for measuring child’s sleep [22].

#### Secondary outcomes

Child development will be measured using the Chinese version of the Ages and Stages Questionnaire—third version (ASQ-3) [24]. ASQ-3 is a developmental screening instrument for children aged 1–66 months and can be administrated by parents [24]. The instrument assesses five developmental domains, including communication, fine motor, gross motor, personal-social, and problem-solving areas. At each time point, each developmental domain will be assessed by six age-specific items. For each item, parents will be instructed to answer “yes”, “sometimes” or “not yet”, and following ASQ-3 procedures [24], the responses will be scored as 10, 5, and 0, respectively. Item scores will be summed to calculate a total sub-score ranging from 0 to 60. The five sub-scores will be totaled to calculate an overall score, ranging from 0 to 300, and higher scores indicate more advanced development. ASQ-3 has been validated against a few professionally administered standardized assessment [24]. Specifically, when compared to the Battelle Developmental Inventory-II, high percent agreements (74%-100%) were observed for the 36-month, 42-month, 48-month, 54-month, and 60-months questionnaires [24].

Children’s executive function will be measured objectively using the Head-Toes-Knees-Shoulders Revised (HTKS-R) task, which is available in the Chinese language [25]. The task is short (around 5–7 min to complete) and requires no special material to administer. It includes four parts and each part includes practice and test items. In part 1, children are asked to say the opposite of the instruction (e.g., “When I say toes, you say head”). In part 2, children are required to do the opposite of what is instructed for a single pair of commands (e.g., “When I say touch your head, you touch your toes” and vice versa). In part 3, another pair of commands is added (e.g., “When I say touch your knees, you touch your shoulders” and vice versa). In part 4, the pairs of commands are switched (e.g., “when I say touch your head, you touch your knees” and vice versa; “when I say touch your toes, you touch your shoulders” and vice versa). The four parts include a total of 59 items, consisting of 22 practice items and 37 test items. For each item, a correct, self-corrected, and incorrect response is scored as 2, 1, and 0, respectively, resulting in a maximum total score of 118. To respond correctly, children need to integrate multiple executive function skills, including working memory (i.e., remembering the rules while listening to the command), inhibitory control (i.e., inhibiting the more natural response to the instruction in favour of the unnatural one), and cognitive flexibility (shifting responses as the rules alternate). A trained research assistant will administer this task with children, who will be accompanied by a parent, via the online conferencing platform. The HTKS has been psychometrically tested in diverse samples of children ages 3 through 6, demonstrating excellent inter-rater reliability (k = 0.9) [25, 26]. A recent study has examined the construction validity of the HTKS-R in pre-schoolers and kindergarteners [25]. The task score was correlated with other measures of working memory (the Auditory Working Memory subtest of the Woodcock-Johnson Tests of Achievement: *r* = 0.19–0.61), inhibitory control (the Day-Night Stroop task: *r* = 0.27–0.43), and cognitive flexibility (the Dimensional Change Card Sort task: *r* = 0.27–0.44) [25].

#### Potential intervention mediators

Targeted mediators of the intervention, including parental attitudes and beliefs towards child sleep behaviours, parental knowledge of the sleep recommendation, self-efficacy, parenting practices, parental modelling, and home environments, will be collected via a parental questionnaire.

#### Covariates

Data on covariates, including child date of birth, gender, number of siblings, and kindergarten attendance, parental year of birth, marital status, and education, household income, grandparent involvement, as well as geographic regions, will be collected via the parental questionnaire.

#### Process evaluation

Fidelity of the intervention will be assessed as attendance rate for each webinar. At the 12-month follow-up, parents in the intervention group will be asked about the acceptability, relevance, and satisfaction of the intervention via a questionnaire.

### Sample size

A sample size calculation was conducted based on repeated MANOVA (two groups, two time points) using G*Power (version 3.1.9.7). To detect a medium effect size (f = 0.25) [27] for the between-groups differences in changes in the primary outcomes, with a power of 0.8 and a Type I error probability of 0.05, the required sample size was calculated to be 128 participants. To further accounted for 20% loss to follow-up, a minimum sample size of 160 participants will be recruited.

### Statistical analysis

To address the primary objective and the secondary objective, a two-level (i.e., level 1 = time, level 2 = subject) model will be employed to examine the intervention effect on each outcome. The model for each outcome will include a random effect of subject and fixed effects of time, group, time*group, and covariates. The beta coefficient for the interaction term “time*group” is interpreted as the difference in changes in the outcome, from 12-month follow-up to baseline timepoints, between intervention and control groups, indicating the intervention effect. To further examine the intervention pathways, multilevel mediation analysis will be used to examine the indirect effects of the intervention on child sleep behaviours through the targeted mediators. Data collected from the pre-intervention interviews will be transcribed verbatim and analysed thematically.

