### Randomisation, allocation, and blinding

Data will be collected at baseline and follow-up (12-month post-baseline). After the baseline assessment, participants will be allocated randomly to the intervention or control groups on a 1:1 ratio by a research assistant not associated with the project. The control group will receive the videos of the educational training sessions after the study ends. The random allocation sequence will be computer generated using SPSS version 26.0 (SPSS Inc., Chicago, IL, USA). Allocation will be blinded for data collectors and participants.

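### For continuous outcomes, the planned difference-in-changes model is valid but does not use the pre-randomisation baseline efficiently; adjusting for it, or constraining it to be equal between arms, gains power at no extra data cost

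*Protocol article*

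**What the plan says.** The Statistical analysis section fixes a two-level model, time within subject, for every outcome: "The model for each outcome will include a random effect of subject and fixed effects of time, group, time*group, and covariates". It reads the time-by-group coefficient as the between-arm difference in change from baseline to 12 months.

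There are only these two assessments, and the first precedes allocation: "After the baseline assessment, participants will be allocated randomly to the intervention or control groups".

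The Covariates section begins "Data on covariates, including child date of birth, gender, number of siblings, and kindergarten attendance" and goes on to parental and household characteristics and region. Most of these are fixed over the trial. The baseline value of the outcome is not among them; it enters the model only as the first of the two repeated responses.

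The Sample size section plans on the same contrast: "To detect a medium effect size (f = 0.25) [27] for the between-groups differences in changes in the primary outcomes". The target is 80% power at alpha 0.05. The section reports that "the required sample size was calculated to be 128 participants" and then allows for "20% loss to follow-up, a minimum sample size of 160 participants will be recruited".

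**The concern.** Because baseline is measured before randomisation, any difference between the arms at that point is chance. The model nevertheless gives that difference its own parameter. With complete data the whole of the observed baseline imbalance is then subtracted from the follow-up difference. When the correlation between the two assessments is below 1, that is more correction than the data warrant, and it adds noise.

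The covariates do not repair this. A time-constant covariate entered as a main effect moves a child's level equally at both times and cancels from the change. A reader who sees an adjusted model would expect the adjustment to improve precision or balance for the treatment effect; here it does almost nothing.

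What is at stake is precision for the continuous sleep and development outcomes, in a trial sized at just 80% power.

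**Working it through.** **Inputs from the protocol.** Effect size f = 0.25 on the difference in changes, alpha 0.05, power 0.80, N = 128, 20% loss and 160 recruited (Sample size); 1:1 allocation after baseline and two assessments (Randomisation, allocation, and blinding).

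**Assumed.** The correlation rho between baseline and 12 months is not given. I use 0.3, 0.5, 0.7 and 0.85. The nearest figures are test–retest reliabilities of 0.62 to 0.79, and 0.85 for the Chinese version (Primary outcome). Their retest interval is not stated, and a 12-month correlation may be lower. I also assume equal outcome variance s² at both times.

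**1. The plan's own figure.** For the time-by-group test, lambda = f² × N = 0.0625 × 128 = 8 with 1 and 126 degrees of freedom. Power is 0.8015 (0.798 at N = 127), so 128 reproduces. 128/0.8 = 160 reproduces too. With two equal groups, f = 0.25 is a difference of 0.5 SD of the change score, so the calculation is a two-sample test on change.

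**2. The planned model behaves as a change-score analysis.** I used three simulated trials of 128 complete pairs (rho 0.5, with a covariate explaining 20% of outcome variance). In each, the time-by-group estimate equalled the raw difference in mean change to four decimals, and adding the covariate left estimate and SE unchanged. In the first trial it was 0.5078 (SE 0.1553) with and without the covariate. With 160 recruited and 20% lost, equality is only approximate: the first such trial moved from 0.4018 (SE 0.1737) to 0.4226 (SE 0.1734).

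**3. Variance with complete data.** Per pair of observations:

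- change score: 2s²(1 − rho)
- baseline-adjusted or common-baseline: s²(1 − rho²)
- ratio: (1 − rho²)/[2(1 − rho)] = (1 + rho)/2

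In the three complete trials, constraining the baseline cut the SE from 0.1553, 0.1839 and 0.1829 to 0.1354, 0.1623 and 0.1573. The squared ratios are 0.76, 0.78 and 0.74, against 0.75 expected. Adding the covariate now helps: 0.1317, 0.1581 and 0.1539.

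**4. Power at 128 completers.** Lambda becomes 8/[(1 + rho)/2], with 1 and 125 degrees of freedom.

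| rho | Variance ratio | Lambda | Planned power | Power using baseline |
|---|---|---|---|---|
| 0.3 | 0.65 | 12.31 | 80.1% | 93.6% |
| 0.5 | 0.75 | 10.67 | 80.1% | 90.0% |
| 0.7 | 0.85 | 9.41 | 80.1% | 86.1% |
| 0.85 | 0.925 | 8.65 | 80.1% | 83.1% |

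**5. Power with 160 recruited and 20% lost at random.** The mixed model keeps baseline-only families, so the planned analysis itself gains a little. With 80 per arm at baseline and 64 at 12 months, the variances are:

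- planned: 2s²[(1 − rho²)/64 + (1 − rho)²/80]
- common baseline: 2s²(1 − rho²)/64

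At rho = 0.5 and s = 1 the difference is 0.5 × √[2(1 − 0.5)] = 0.5. The SEs are √0.02969 = 0.1723 and √0.02344 = 0.1531. Normal-approximation power is Φ(0.5/0.1723 − 1.96) = 82.7% and Φ(0.5/0.1531 − 1.96) = 90.4%.

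Generalised least squares with losses drawn at random (arms not split exactly 64/64; the balanced formulas agree within about 0.3 points) gave:

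| rho | Planned | Common baseline |
|---|---|---|
| 0.3 | 83.4% | 93.8% |
| 0.5 | 82.7% | 90.4% |
| 0.7 | 81.9% | 86.6% |
| 0.85 | 81.1% | 83.4% |

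On this approximation 128 completers alone give the planned analysis 80.7%.

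**6. Other reading of the effect size.** If 0.5 SD meant the outcome's SD rather than that of change, power at 128 completers (normal approximation) would go from 66.7% to 84.3% at rho 0.3, 80.7% to 90.4% at 0.5, and 95.5% to 97.7% at 0.7. The direction is the same.

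**The case against.** The strongest reply is that nothing here is wrong. The hypotheses are worded as greater increase and greater improvement, the sample size is built on differences in change, and the model tests that contrast. The estimate is unbiased under randomisation and the stated power is delivered. All of that stands: a reader might infer from the point that the planned result would be biased or underpowered, and the protocol does not support that.

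Three other strong readings also fail.

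- **A fixed gain.** A reader might infer that power would rise to 86–94%. That range needs rho between 0.3 and 0.7, which the protocol nowhere states. At 0.85, the highest reliability it quotes, the gain is about 3 points for completers and about 2 once the expected loss is included.
- **Covariates that do nothing at all.** This is exact only for a linear model, complete data and time-constant covariates. With loss they shift the estimate slightly, and kindergarten attendance, income or grandparent involvement could vary if re-measured, which the protocol does not say.
- **One result for every outcome.** The first hypothesis concerns the proportion meeting the sleep-duration recommendation. Neither the variance ratio nor the covariate result carries over exactly to a binary model.

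**Conclusion.** The point holds as an improvement to a stated method, not as an error. For continuous outcomes, using the baseline as a covariate or as a common mean reduces the variance for any rho below 1, at the price of about one degree of freedom in the regression form. With the planned recruitment and loss, the gain is roughly 10, 8, 5 and 2 percentage points of power at rho 0.3, 0.5, 0.7 and 0.85.

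These sizes rest on the assumed rho, equal variances at the two times, loss at random, and an effect of 0.5 SD of change. The justification for a common baseline rests on allocation following the baseline assessment, which the protocol states. The change is best fixed before outcome data are seen, so that there is no later choice between change-score and baseline-adjusted results.

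**What to change.** For continuous outcomes, replace the model sentence with one of two forms.

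1. **Constrained longitudinal model.** Include time, a treatment indicator equal to 1 only for the intervention arm at 12 months, covariates and an unstructured 2×2 covariance. Keep participants who have baseline data only.
2. **Regression of the 12-month value** on group, baseline value and covariates. This is simpler, but in ordinary form it drops families without follow-up.

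Spell out the indicator in form 1. Merely deleting the group main effect is not enough when time and group are coded as factors: software then refits the same model (the log-likelihood was identical in a check), and the 12-month coefficient becomes the raw follow-up difference. Time interactions for age and sex are optional; covariates already contribute once the baseline is constrained.

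For the binary adherence outcome, adjust for baseline adherence status in a suitable binary model, and do not quote the gains above for it.

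The cost is a few lines in the analysis section. No new data, participants or software are needed, and the sample size can stay as it is.

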### Ethics, data management, and dissemination

Ethical approval for the study was obtained from the Beijing Normal University Faculty of Education Research Ethics Committee (IRB Number: BNU202212100058). After eligibility screening, parents will be required to provide written informed consent for their own and their child’s participation in the study. Participants will be informed that their participation is voluntary and they can withdraw without penalty at any time. The likelihood and extent of potential harm resulting from participation are not anticipated to exceed those encountered in participants’ daily lives related to the study. To minimize the burden on participating families, we will not collect data on adverse events. Identifying information will be collected through the consent form and each participant will be assigned a unique participant number. Collected data will be linked to participant numbers, not identifying information. Data will be stored on password-protected computers, with access limited to the research team. A master file containing participant numbers and identifying information will be destroyed securely at the conclusion of data collection. Deidentified data will be retained for a minimum of ten years after study completion. The study findings will be disseminated through peer-reviewed publications, presentations at academic and professional conferences, as well as social and traditional medias. These knowledge translation activities will be of general findings and will not breach individual confidentiality.

## Discussion

Early childhood is a period when sleep patterns evolved most rapidly [28]. Sleep patterns during the pre-school period are relatively more stable compared to infancy and toddlerhood but continue to change [28]. Unhealthy sleep patterns formed in the early years tend to track into later childhood and have long-lasting effects on health and development [14]. Inadequate and poor sleep were observed in a large proportion of kindergarteners in China [12, 13], warranting interventions targeting this population. However, in a recent published systematic review on sleep interventions for young children, no studies have been conducted in China [16]. The study described in the present protocol will be, to our best knowledge, the first intervention promoting healthy sleep among kindergarteners in China and is developed with an evidence-based and theory-driven approach. This intervention will be centred around family units, given evidence on the important role of family settings and parental factors in shaping young children’s sleep behaviours [29]. The design of intervention components is guided by the SCT to support parents as the change agent [18, 19]. To increase relevance, the content of the intervention is tailored to cultural contexts and will be refined according to the pre-intervention interviews. Findings from this intervention will provide important insights on effective strategies for parents, especially those from Chinese cultural backgrounds, to help their child establish healthy sleep habits. Moreover, this intervention is online-based and, if efficacious, has the potential to be offered widely to parents, including those residing in rural and remote areas, to support them in promoting healthy sleep for their child from the earliest years of life.

This study will use a rigorous research design to examine the intervention effects on development outcomes and the mediating role of sleep. The findings can provide high-quality evidence on sleep in relation to development outcomes in kindergarteners from low- and middle-income countries. This evidence will be important to inform the international and national updates of the sleep recommendation as the development of current sleep recommendations was based on evidence that relied heavily on observational studies conducted in high-income countries [17]. Findings from this study also have the potential to inform effective strategies and programs to support healthy development in children from Chinese cultural backgrounds.

## Data Availability

Not applicable.

## Abbreviations

ASQ-3: Ages and Stages Questionnaire – third version
BCT: Behaviour Change Technique
CSHQ: Children’s Sleep Habit Questionnaire
HTKS-R: Head-Toes-Knees-Shoulders Revised
RCT: Randomised Controlled Trial
SCT: Social Cognitive Theory
WHO: World Health Organisation
